## Abstract

**Background:**

The age- and gender-specific incidence of total hip replacement surgery has increased over the last two decades in all age groups. Recent studies indicate that non-surgical interventions are effective in reducing pain and disability, even at later stages of the disease when joint replacement is considered. We hypothesize that the time to hip replacement can be postponed in patients with severe hip osteoarthritis following participation in a patient education and supervised exercise program when compared to patients receiving patient education alone.

**Methods/design:**

A prospective, blinded, parallel-group multi-center trial (2 sites), with balanced randomization [1:1]. Patients with hip osteoarthritis and an indication for hip replacement surgery, aged 40 years and above, will be consecutively recruited and randomized into two treatment groups. The active treatment group will receive 3 months of supervised exercise consisting of 12 sessions of individualized, goal-based neuromuscular training, and 12 sessions of intensive resistance training plus patient education (3 sessions). The control group will receive only patient education (3 sessions). The primary end-point for assessing the effectiveness of the intervention is 12 months after baseline. However, follow-ups will also be performed once a year for at least 5 years. The *primary* outcome measure is the time to hip replacement surgery measured on a Kaplain-Meier survival curve from time of inclusion. *Secondary* outcome measures are the five subscales of the Hip disability and Osteoarthritis Outcome Score, physical activity level (UCLA activity score), and patient’s global perceived effect. *Other* measures include pain after exercise, joint-specific adverse events, exercise adherence, general health status (EQ-5D-5L), mechanical muscle strength and performance in physical tests. A cost-effectiveness analysis will also be performed.

**Discussion:**

To our knowledge, this is the first randomized clinical trial comparing a patient education plus supervised exercise program to patient education alone in hip osteoarthritis patients with an indication for surgery on the time to total hip replacement.

**Trial registration:**

NCT01697241

## Background

Osteoarthritis (OA) is the most common joint disease and a major contributor to pain, decreased physical function and decline in health-related quality of life [1]. Its incidence and prevalence will increase in the coming years due to the ageing of the population [2]. Already, the incidence of total hip replacement in Denmark, has increased from 75 per 100,000 in 1995 to 170 per 100,000 in 2009 [3], a development likely to continue as joint replacements are generally recommended at later stages of the disease and therefore, commonly experienced as one gets older. Such a development has socio-economic consequences, and thus, calls for potential non-surgical treatment alternatives, especially those which are effective in improving physical function and reducing pain to a level where health-related quality of life is restored, and the need for total joint replacement is at best eliminated, or at least, postponed.

Within the last decade, it has become well established that exercise reduces pain and improves function in patients with knee OA [4-12]. A recent meta-analysis on supervised exercise interventions showed that exercise had moderate effect on pain and self-reported physical function in patients with mild to moderate knee OA [11], and another meta-analysis found similar effects in those waiting for knee replacement [4]. Supported by these meta-analyses, exercise is recommended in clinical guidelines for the management of knee OA across the severity range of the disease [10]. Conversely, evidence to support exercise as part of the management of hip OA is lacking, primarily due to the absence of hip-specific studies [6,9,13]. Randomized Controlled Trials (RCTs) of exercise specific to hip OA are one of the top research priorities of the European League against Rheumatism (EULAR) [14].

Exercise treatment could potentially be used to postpone hip replacement surgery. Although, the optimal type of exercise is yet to be determined. An individualized approach to exercise prescription is needed based on assessment of impairments [10]. In addition, exercise classes are more effective in reducing pain than home-based programs [15], and both the progression and intensity should be carefully controlled as they are the strongest factors affecting functional outcome [16,17]. Hence, an exercise intervention aimed at postponing or eliminating surgery should be individualized, class-based, progression-controlled, and feasible for patients with severe hip OA.

A program based on neuromuscular principles was found to be feasible in elderly patients scheduled for hip and knee replacement, and it complied with the above recommendations for exercise prescription [18], while intensive resistance training has proven effective in hip patients in the early postoperative phase [19]. To mimic performance enhancement in sports, and possibly to boost the effect of the intervention, both exercise modalities will be used in this trial.

In summary, more evidence to support the use of exercise as non-surgical treatment in the management of patients with severe hip OA is needed, and its effect on the time to hip replacement surgery is largely unknown.

### Specific objective and hypothesis

The *primary* aim is to test the hypothesis that patients with severe hip OA are more likely to postpone hip replacement surgery following participation in a patient education and supervised exercise program when compared to patients receiving patient education alone. The *secondary* aim is to examine if self-reported musculoskeletal health defined as pain, physical function, physical activity and quality of life (HOOS), physical activity level (UCLA activity score), and the patient’s global perceived effect (GPE) improve more in the education and exercise group. *Other* measures include pain after exercise, joint-specific adverse events, exercise adherence, general health status (EQ-5D-5L), mechanical muscle strength and physical performance tests. A cost-effectiveness analysis will also be performed.

## Methods and materials

### Study design

A prospective, blinded, parallel-group, multi–center trial (2 sites), with balanced randomization [1:1], in accordance with CONSORT (Consolidated Standards of Reporting Trials) guidelines [20].

### Participants and recruitment procedures

Patients aged 40 years and older with an indication for total hip replacement (THR) for hip OA will be consecutively recruited from the outpatient clinic at the Department of Orthopedic Surgery and Traumatology, Odense University Hospital, and Vejle Hospital, Denmark. The inclusion and exclusion criteria are listed in Table 1. The indication for THR will be based upon symptoms, a clinical examination and radiographic findings [21]. Although, defining the cut points for symptoms and functional disability which indicate the need for a hip replacement is complex [22]. Data on multiple other factors such as home situation, co-morbidities, and marital status will be collected at baseline. An independent radiologist will assess the stage of hip OA severity using the Kellgren-Lawrence grading scale [23].

**Table 1 T1:** Criteria for participants in the study

**Inclusion criteria**	**Exclusion criteria**
40 years and older	Inflammatory joint disease
Indication for total hip replacement	Earlier ipsilateral proximal femur fracture
Residency within local municipality or willing to commute	Hip pain < 3 months
	Neuropathy or neuromuscular disease
	Malignant disease
	Diseases where a moderate level of physical exercise is contraindicated
	Inability to speak or read Danish
	Inability to participate for other reasons
	Refusal to participate

On initial contact, patients will be examined and an indication for hip surgery will be assessed by an orthopedic surgeon. Where all inclusion criteria and none of the exclusion criteria are met, the patients will be invited to participate and will receive verbal and written information about the trial (background, procedure, randomization, and potential risks). In addition, a standardized information video without technical or value-laden terms will be provided to patients to ensure impartiality between treatments and consistency at both hospitals. Information will be given in an undisturbed location within the outpatient clinic, and time will be made available for questions. Subsequently, the patients will receive the written consent form. Patients wishing to have some reflection time will be given a stamped addressed envelope, and contacted by the research nurse no later than 2 days after consultation. Patients who choose not to have reflection time will sign the written consent form, be randomized, and scheduled for the completion of baseline measurements.

A flow diagram of the progress (enrolment, randomization, intervention allocation, and follow-up and data analysis) through the trial can be found in Figure 1.

**Figure 1 F1:**
[figure not shown]
Study flow chart through-out the randomized clinical trial.

### Interventions

The active treatment group (EDU+EX) will consist of patient education and supervised exercise. The control group (EDU) will consist of patient education only. Patients in group EDU+EX will receive two types of exercise, delivered on separate days. One type of exercise is class-based, individualized, goal-oriented NEuroMuscular EXercise training for patients who are scheduled for total joint replacement (NEMEX-TJR). The other type of exercise will be class-based, individualized, intensive Resistance Training (RT). Both groups will receive education, which will be administered on separate days to ensure that EDU+EX patients receive education independently from patients randomized to EDU.

#### The NEMEX-TJR exercise program

The aim of NEMEX-TJR training is to improve sensorimotor control and achieve compensatory functional stability. Functional, weight-bearing exercises are used in various positions, resembling conditions of daily living and more strenuous activities [18]. The program emphasizes neutral alignment of the hip, knee and foot, and although focus is on the affected leg, exercises are carried out with both legs. Progression is guided by the patient’s neuromuscular function [18] to accommodate the individual’s level of function and pain. The NEMEX-TJR program has previously been described in detail and is available for download as an additional file [18].

#### The RT exercise program

The aim of intensive resistance training is to improve functional capacity through improvements in muscle strength and power. Progression in these exercises is guided by load [24]. Thus, the quantity of muscle output and the stimulation of neural adaptation (neural drive) is emphasized. Multiple and single joint, non-weight-bearing exercises targeting isolated muscle groups are used. Each exercise is performed as three sets of 8–12 repetitions equal to 70-80% of 1 Repetition Maximum (RM) with time for rest equivalent to that of one set [25-27].

Each of the two types of exercise will be offered weekly during the 12-week intervention period in sessions lasting 60–70 minutes. Thus, the entire exercise intervention will consist of 24 sessions, and the patients will be admitted continuously into the class-based groups so each group consists of both novice and experienced participants. Exercise professionals who are experienced in the execution of both types of exercise will be responsible for the patient education and supervised exercise program.

Both types of exercise may provoke pain and patients will therefore be asked to rate their pain intensity (0=no pain, 10=worst possible pain) before and after each session on a visual analogue scale (VAS). In accordance with the NEXEM-TJR program the patients will be told that pain up to a level of 5 is considered “acceptable” after each training session. The day after training, their pain should subside to ‘pain as usual’ and not increase over time. ‘Pain as usual’ is defined as the pain level prior to exercise. If this does not occur, the level of training progression will be reduced [18].

#### The patient education program

The patient education program is designed to encourage the patient to actively engage in and take responsibility for the management and treatment of their hip OA. The program is called GLA:D (Good Life with Arthritis in Denmark), and is based on principles used in The Osteoarthritis Management Course developed in Sweden (BOA, Gothenburg, Sweden) [28]. It consists of three sessions, each with a duration of 90 minutes. The content of the program has been translated into Danish and found to be feasible. All physiotherapists will attend a course in delivering the GLA:D concept to ensure consistency. Sessions will be held in groups of up to 15 participants. The physiotherapists responsible for conducting the program will facilitate interaction and discussions between the patients. The education group will be similarly monitored to the supervised exercise group.

### Intervention and follow-up period

Assessments will be made at baseline, 3 and 12 months after randomization, and both treatment groups will have completed the intervention after 3 months [29]. After the intervention, patients will be encouraged to continue the exercise program unsupervised at home or in public fitness centers.

### Outcome measures

One primary outcome measure has been chosen to avoid problems of interpretation associated with multiplicity of analysis [30,31]. It will be supported by a range of self-reported secondary outcome measures.

### Primary outcome measure

Cumulative Survival analysis (Kaplan-Meier survival curve).

Cumulative survival is measured as the time in days without total hip replacement surgery since inclusion.

### Secondary outcome measures

#### The Hip disability and Osteoarthritis Outcome Score (HOOS 2.0)

HOOS is a patient-reported outcome measure with five subscales for pain, other symptoms, function in daily living, function in sport and recreation and health-related quality of life (QoL) [32]. A 5-point Likert-scale will be used and converted into a 100-point scale with zero indicating the worst possible health [33].

#### Physical activity level

The University of California Los Angeles activity score (UCLA activity score) is a 10-point Likert scale recommended and used extensively in similar populations [34,35].

#### Global perceived effect (GPE) score

In addition to pain and physical function, the assessment by the patient of a global perceived effect of the treatment is a recommended responder criterion [36]. Patients will be asked to rate possible change in their condition (pain, symptoms, ADL, sport and recreation, QoL, level of physical activity, treatment evaluation) since the initial administration (baseline) on a 7-point Likert scale. A 2-point change from ‘no change’ will be used as cut-off to categorize the response into: 1) better, 2) no change, and 3) worse, with ‘no change’ being the neutral response.

### Other measures

#### Self-reported exercise pain

Pain will be self-reported immediately before and after each exercise session using a VAS scale. Pain scores will be grouped into 0–2 indicating safe, > 2-5 acceptable, and > 5 high risk pain [18]. Self-reported pain after exercise will be used to rate the overall percentage of training sessions completed with acceptable pain, and to evaluate joint-specific adverse events (detailed later).

#### Exercise adherence

‘The extent to which a person’s behavior corresponds with agreed recommendations from a health care provider’ [37]. Adherence will be measured as the number of training sessions completed out of the expected 24 sessions, and will be analyzed separately for RT and NEMEX exercises. Excellent adherence will be defined as participation in 75% or more of the exercise sessions, good as 50-74%, moderate as 25-49%, and poor when participation in less than 25% of the sessions. Patients ceasing training or unwilling to continue will be referred back to the orthopedic department for an optional total joint replacement without having to enter into possible waiting lists.

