### Sample size

One year has been selected as a clinically relevant period to postpone surgery. The survival probability in the education plus exercise group at one year is estimated to be 0.80 and 0.60 for the education only group. Survival group differences will be tested using log-rank statistics. To achieve a statistical power of 80% (β=0.20), the estimated sample size for a two-sample comparison (days without surgery) of survivor functions (log-rank), a sample size of n=86 is needed in each group to detect statistically significant differences (for α=0.05). Allowing for no more than 15% drop-out, 200 patients in total will be recruited.

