### Statistical analysis

All outcome measures will be checked for Gaussian distribution, and non-parametric data will be analyzed using a Mann–Whitney rank sum test [41]. The treatment effect will be analyzed using a random effects mixed linear model (repeated measures) [42]. Hence, correlated measurements from the same patient can be modeled. Model assumptions are checked by residual plots and the model includes the interaction between treatment and elapsed time, adjusted for baseline values. All analysis will follow the intention-to-treat principle [43]. However, subsequent analysis using last observation carried forward may be required. Finally, the number needed to treat (NNT) for a positive effect of treatment (no surgery after 1 year) will be analyzed. All statistical analyses are blinded and will be performed using Stata 11 software (StataCorp, TX, USA).

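### Surgery without a waiting list is offered only to patients who stop training, so any queue would shift early operation times slightly against exercise

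*Protocol article*

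**What the plan says.** Under Exercise adherence, the Protocol article first defines adherence as sessions completed out of 24. It then says that patients who stop training, or do not want to go on with it, are "referred back to the orthopedic department for an optional total joint replacement without having to enter into possible waiting lists".

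Under Interventions, the comparator is defined: "The control group (EDU) will consist of patient education only". Those patients have no training to cease.

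Under Primary outcome measure: "Cumulative survival is measured as the time in days without total hip replacement surgery since inclusion". The event is therefore the operation, not the decision to have it.

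The only statement about parallel handling of the control arm is in the section on the patient education program: "The education group will be similarly monitored to the supervised exercise group". It concerns monitoring, not access to surgery. The article gives no queue length and calls waiting lists only possible.

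**The concern.** Every participant already has an indication for hip replacement. Once a patient decides on surgery, any time spent waiting for a slot counts as surgery-free time. If exercise patients who stop training skip the wait and education-only patients do not, two patients who decide on the same day have different event times because of their arm.

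The log-rank test uses the order of events, so this shifts the statistic. It also shapes the early Kaplan-Meier curve: the exercise arm can show more operations than control in the first months even though fewer exercise patients have chosen surgery. The article plans long-term follow-up of the same patients, so that early segment would stay in later curves too.

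**Working it through.** **Inputs from the Protocol article.** One-year surgery-free probabilities (Sample size): "The survival probability in the education plus exercise group at one year is estimated to be 0.80 and 0.60 for the education only group". Also from that section: log-rank test, 80% power, α = 0.05, 86 per group, 15% drop-out, 200 in total. Training lasts 12 weeks, taken as 84 days.

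**Assumptions.** A fixed queue q of 1, 2 or 3 months (30.4, 60.9 or 91.3 days). Decision times are exponential. Every exercise patient who decides within 84 days stops training and skips the queue; everyone else waits q days. Taking all early deciders as bypassing makes this an upper bound for a given q.

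**The plan's own figure.** Freedman's formula gives a hazard ratio of ln 0.80 / ln 0.60 = 0.437. Events = (1.96 + 0.84)² × [(1 + 0.437)/(1 − 0.437)]² ≈ 51.1. Total expected event proportion over the two groups is 0.20 + 0.40 = 0.60, so n per group = 51.1/0.60 = 85.2, rounded up to 86. The stated size reproduces with a two-sided 0.05.

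**Calibration.** The 0.80 and 0.60 describe time without surgery, so they must hold with the queue included. The probability of no decision by time t is then 0.80^(t/(365.25 − q)) for exercise and 0.60^(t/(365.25 − q)) for control.

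**Exercise patients affected.** The share deciding within 84 days is 1 − 0.80^(84/(365.25 − q)):
- q = 1 month: 1 − 0.80^(84/334.85) = 5.4%
- q = 2 months: 1 − 0.80^(84/304.35) = 6.0%
- q = 3 months: 1 − 0.80^(84/273.95) = 6.6%

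Each is operated q days sooner, so mean surgery-free time in the exercise arm falls by share × q: about 1.7, 3.6 and 6.0 days.

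**Shape of the early curve, 2-month queue, day 84.**
- Exercise, operated: 6.0%
- Control, operated: 1 − 0.60^((84 − 60.9)/304.35) = 3.8%
- Control, decided: 1 − 0.60^(84/304.35) = 13.1%

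The curves put exercise behind control at a point where the decisions point the other way. The exercise arm shows more operations until the curves cross. For q = 1 month this is at q × ln 0.6/(ln 0.6 − ln 0.8) = day 54. For q = 2 and 3 months it is at q + 84 × ln 0.8/ln 0.6 = day 98 and day 128. The distortion ends at 84 + q: day 114, 145 and 175.

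**One year.** Because 84 + q is below 365 days, every patient who bypasses would have been operated within the year anyway. One-year survival stays at 0.80 and 0.60, and the number needed to treat stays at 1/(0.80 − 0.60) = 5.

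**Log-rank test.** Simulated with 100 per arm, 15% exponential drop-out, censoring at 365.25 days and the same random numbers under both rules. The null case sets 0.60 in both arms.

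| Queue | Power, equal queue | Power, bypass | False results favouring control, equal queue | Same, bypass |
|---|---|---|---|---|
| 1 month | about 85% | about 84% | about 2.5% | about 2.9% |
| 2 months | about 85% | about 83% | about 2.5% | about 3.3% |
| 3 months | about 85% | about 82% | about 2.5% | about 3.9% |

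A repeat with 40,000 replicates agreed to about 0.1 point on the error rates and gave power losses of about 1, 2 and 3 points. With 86 per arm and no drop-out, power with the bypass is about 0.83, 0.81 and 0.80, against 0.83 to 0.84 with equal queues. A 6-month queue would bring it to about 0.78.

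**The case against.** The strongest reply is that this rests on silence in a condensed article. The text never says that education-only patients must queue, and the full protocol may give them the same route. The phrase about being unwilling to continue might even be stretched to cover them. Waiting lists are called only possible, and with no queue there is no effect. The rule is also a sensible safeguard: patients who try exercise first should not lose time by it.

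Part of this stands. The effect is conditional, and one sentence from the full protocol could close the point. But the article does not merely omit a detail. It states a rule on access to surgery, under an exercise heading and in terms of training, in a trial whose endpoint is the date of surgery.

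A reader might go further and infer that the trial is underpowered. If 0.80 and 0.60 are attached to the decision date and a queue is added on top, power with the bypass comes out at 81.8%, 77.6% and 72.8% for 1, 2 and 3 months. The document does not support that calibration, because its probabilities are for time without surgery. Most of that fall also comes from the queue itself: power is 85.6% with no queue and already 82.8%, 79.5% and 75.5% with equal queues.

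Nor does the text say that all exercise patients skip the queue all year, which would cut power far more. The rule covers those who stop training.

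**Conclusion.** The point holds as a minor one. As written, the rule times operations differently by arm if a queue exists and control patients join it. For assumed queues of 1 to 3 months it costs about 1 to 3 points of power, leaves power above 80% at the planned recruitment, and raises false results favouring control by about 0.4 to 1.4 points. The loss is smaller if the queue is shorter, if only some early deciders use the bypass, or if controls also skip it.

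The direction is conservative, so the rule cannot manufacture a benefit of exercise. The 12-month survival probabilities are untouched, and so is the planned summary: "the number needed to treat (NNT) for a positive effect of treatment (no surgery after 1 year) will be analyzed". What is affected is the early Kaplan-Meier curve and, slightly, the log-rank test. Confidence is medium, because the existence and length of a queue and the control arm's route to surgery are not documented.

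**What to change.** Under Exercise adherence, or better in a section that covers both arms, state that any patient in either arm who asks for surgery gets the same access without waiting lists. This keeps the exit for exercise patients and extends it to controls.

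Record in both arms the date on which surgery is decided or listed, and prespecify a log-rank sensitivity analysis on that date. Keep the operation date as the primary endpoint: the decision date is softer, and neither patients nor health care providers are blinded.

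The cost is one extra date per patient who chooses surgery, one extra analysis, and agreement from the two hospitals to equal access.
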